### Support for the cancer exercise specialists

A certified cancer exercise specialist is an advanced fitness instructor with a level 4 vocational qualification, according to the Regulated Qualifications Framework in the UK, in designing and delivering oncology exercise programmes. The three cancer exercise specialists involved in the present study also hold other vocational health and fitness qualifications and one is enrolled on an MSc in Cancer Care degree programme. All the cancer exercise specialists performed a similar role as for the present study working on the SafeFit trial [62]. They already have received training from a chartered psychologist ([name]) in motivational interviewing and other behaviour change techniques. The training involved two, 2-hour workshops and included a bespoke workbook that contains content from workshop presentation slides, practical activities, scenario-based learning activities, action and coping planning sheets, and self-reflective diary sheets. The cancer exercise specialists also met with the chartered psychologist for 1 hour at another two time points during working with their first patient to obtain further support in applying the motivational interviewing and other behaviour change techniques. Exercise programme design and delivery by the cancer exercise specialists will be undertaken with the guidance and supervision (including fidelity checks) of a certified exercise physiologist ([name]) via fortnightly meetings throughout the study period.

### Outcome measures

Primary quantitative outcome. Retention: Percentage of patients that completed the 8-week exercise programme.

### Secondary quantitative outcomes

Exercise uptake: percentage of eligible patients that agreed to participate in the exercise programme. Reasons for refusal will be documented where possible.Exercise adherence (based on the definitions proposed by Nilsen et al. [63]):
Exercise programme adherence: percentage of the total prescribed training sessions engaged in.Exercise programme interruption: percentage of patients that missed at least three continuous scheduled training sessions.Pre-session dose modification: number of training sessions where the exercise dose was modified before starting the training session.During session dose modification: number of training sessions where the exercise dose was modified during the training session.Early session termination: number of training sessions terminated early by the patients.Pre- and post-intervention patient-reported measures of fatigue (MFSI-SF), quality of life (SF-36), and physical activity levels (IPAQ-SF).Pre- and post-intervention measures of physical fitness: aerobic endurance (6-Minute Walk Test), upper and lower body muscular strength and endurance (Arm Curl Test and 30-Second Chair Stand Test), power, speed, agility, and dynamic balance (8-Foot Up-and-Go Test), and flexibility (goniometric measures of neck and shoulder range of motion).Frequency, intensity, duration, type, and location, of exercise, and the starting point of the exercise programme (i.e., before, during, or after treatment).

Qualitative outcomes. Acceptability, processes, and integration of the intervention into the usual care pathway will be evaluated by interviewing a sample of patients, health care professionals, and the cancer exercise specialists.

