Resistance exercise	**Frequency**: ≥ 2 days/week. Advise twice per week where possible. If a participant refuses to perform aerobic exercise, advise 3 days/week. **Intensity**: 8–15 repetitions (≥ 60% 1RM). Advise 10–15 repetitions for deconditioned/currently sedentary individuals. **Time:** For deconditioned/currently sedentary individuals, prescribe 1 set per exercise for the first 2 weeks and progress to 2 sets thereafter. Rest 2–3 minutes between sets. **Type**: Dynamic exercises using both concentric and eccentric muscle actions, although a combination of dynamic and isometric exercise can be performed if isometric exercise is not contraindicated. All major muscles groups should be exercised, preferably using multijoint exercises. **Pattern:** Spread sessions evenly throughout the week, with at least 48 hr recovery before exercising the same muscle groups again. **Progression:** Use the double progressive method [55]. This initially involves increasing the repetitions within the target repetition range. Once the patient can perform the maximum number of repetitions within the target repetition range for all sets for a given exercise, with good form, the resistance is increased. When using exercise bands, the patient should be instructed on the importance of standardising hand placement on the band. Hands that are further apart on the band will increase resistance, and vice-versa. **Miscellaneous:** The resistance training programme should include 8–10 different exercises using a whole-body approach. Split routines should be avoided unless the participant has recent (within the last 4 weeks) resistance training experience, and it is inappropriate for the volume of resistance exercise to be fit into one training bout. Exercises that target specific muscles should be incorporated into the training programme where dysfunction from treatment is interfering with the ability to undertake activities of daily living. Multijoint exercises and large muscle groups should be exercised before single joint and smaller muscle groups in each exercise session.

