Flexibility exercise	**Frequency:** ≥ 2 days/week on days when other exercise is being performed. **Intensity:** Stretch to a feeling of tightness or slight discomfort. **Time:** 8–10 stretches each held for 10–15 sec for maintenance stretches and 30 sec for developmental stretches. **Type:** Static stretches for major muscle groups, focusing more time on any muscles that have been found to be shorter than the normal range, especially if causing physical dysfunction.

Balance exercises also will be encouraged for any patients that present with balance issues during their initial assessments [53]. Patients’ needs, preferences, and goals will take precedence, however, if these are not congruent with current physical activity guidelines. This approach is based on the premise that the best exercises are the ones the person will do. Personalisation of exercise programmes will include appropriate manipulation of the frequency, intensity, time, type, volume, progression, and location of the exercise [54]. A menu of no-cost, convenient, locally available, or virtual exercise options, partly informed by previous research [14], will be used to help patients choose their preferred type of exercise and location. However, patients will be encouraged to suggest alternatives based on preferences and any past successes at adhering to exercise. The exercise location is therefore likely to differ based on patient preference. Whether patients exercise alone or with others also will largely depend on personal preference. Supervised group exercise sessions will not be offered due to increased expense and funding restrictions. Flexibility will be embedded into each patient’s exercise programme so that they can autoregulate the acute training variables in response to changes in symptoms and other perceived barriers to exercise [34]. Coloured elastic resistance bands (Theraband, Akron, OH) will be given to patients for performing resistance exercises. Each colour represents a different band resistance at 100% elongation (i.e., tan = 1.1 kg, yellow = 1.3 kg, red = 1.7 kg, green = 2.1 kg, purple = 2.6 kg, black = 3.3 kg, silver = 4.6 kg, and gold = 6.5 kg). Resistance bands have been shown to be a versatile and effective method for developing muscular strength and endurance compared to the use of conventional resistance training equipment such as free weights and resistance training machines [56].

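### Three exercise-adherence outcomes are bare session counts, so they mix how often sessions are modified or cut short with how many sessions each patient had

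*Protocol article*

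**What the plan says.** The protocol article lists five exercise-adherence measures under Secondary quantitative outcomes. Two carry a denominator:

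- Programme adherence is the "percentage of the total prescribed training sessions engaged in".
- Programme interruption is the "percentage of patients that missed at least three continuous scheduled training sessions".

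The other three do not:

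- Pre-session dose modification is the "number of training sessions where the exercise dose was modified before starting the training session".
- During-session dose modification is the "number of training sessions where the exercise dose was modified during the training session".
- Early session termination is the "number of training sessions terminated early by the patients".

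The number of sessions per patient is left open. The Study intervention section says: "Personalisation of exercise programmes will include appropriate manipulation of the frequency, intensity, time, type, volume, progression, and location of the exercise". It adds: "Patients’ needs, preferences, and goals will take precedence, however, if these are not congruent with current physical activity guidelines". Table 2 gives minimum weekly frequencies (aerobic at least 3 days, resistance at least 2) and varies them with the patient's choices, for example: "If a participant refuses to perform aerobic exercise, advise 3 days/week".

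The Participants section plans on 60% retention of 70 recruits. The Recruitment section says that the influence of start time on adherence will be examined. Data analyses offers generic summaries, percentages among them, with 95% confidence intervals, and ties none of them to sessions prescribed or started.

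**The concern.** A count of events is interpretable on its own only when everyone has about the same opportunity to have the event. Here the opportunity differs by design. One patient may agree a programme with few weekly sessions and another with many, and some will leave before week 8. A low count can mean that sessions were seldom changed, that few were prescribed, or that the patient left early.

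At stake is the use of these outcomes across start times. If patients starting at one point in the pathway are prescribed fewer sessions or leave sooner than those starting at another, their counts fall for that reason alone. The planned evaluation by start time would then compare exposure as well as behaviour. Patients' adjustment of their own training is also a built-in feature of the intervention. How often it is used is something the future trial would want to know, and a frequency of use needs a denominator.

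**Working it through.** **The plan's own figures.** The article gives no figure for these three outcomes. The relevant planning figure reproduces: 70 × 0.60 = 42 completers, which leaves room for 70 − 42 = 28 non-completers (40%).

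**Inputs.** The programme length of 8 weeks is from the article. The sessions per week (2, 3, 5), the stopping weeks (2, 4) and the per-session modification rate (25%, range 10% to 40%) are assumptions, because the article fixes none of them. Every scheduled session is taken as started. Aerobic and resistance work may share a day, so 5 per week is only one possible schedule.

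**Step 1: expected count.** Expected count = rate × sessions per week × weeks attended.

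| Patient | Sessions | Count at 10% | Count at 25% | Count at 40% |
|---|---|---|---|---|
| 5/week, completes | 40 | 4.0 | 10.0 | 16.0 |
| 3/week, completes | 24 | 2.4 | 6.0 | 9.6 |
| 2/week, completes | 16 | 1.6 | 4.0 | 6.4 |
| 5/week, stops after week 4 | 20 | 2.0 | 5.0 | 8.0 |
| 5/week, stops after week 2 | 10 | 1.0 | 2.5 | 4.0 |
| 3/week, stops after week 2 | 6 | 0.6 | 1.5 | 2.4 |

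Within a column the rate is identical. Frequency alone produces a 40/16 = 2.5-fold gap among completers. Stopping after week 2 produces an 8/2 = 4-fold gap at any given frequency. Neither ratio depends on the assumed rate.

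**Step 2: reading a count backwards.** A count of 6 means 6/16 = 37.5% of sessions at 2 per week, 6/24 = 25% at 3 per week and 6/40 = 15% at 5 per week.

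**Step 3: order can reverse.** A patient who modifies 50% of 10 sessions scores 5. A completer who modifies 20% of 40 sessions scores 8. The patient who modifies more often has the lower count.

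**Step 4: group level.** Take 5 sessions per week, a 25% rate and drop-outs leaving after week 2.

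- At 60% retention: 0.25 × (0.6 × 40 + 0.4 × 10) = 0.25 × 28 = 7.0 per patient, or 490 among 70 patients.
- At 90% retention: 0.25 × (0.9 × 40 + 0.1 × 10) = 0.25 × 37 = 9.25 per patient, or 647.5 among 70.

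With drop-out after week 4 the means are 8.0 and 9.5. Worse retention lowers the count, as a mean or as a total, although the rate has not changed.

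**Step 5: choice of denominator.** For the patient at 3 per week who stops after week 2, dividing by the sessions actually available gives 1.5/6 = 25%, the true rate. Dividing by the full 8-week prescription gives 1.5/24 = 6.25%, so the effect of drop-out stays in the figure. The denominator must stop at withdrawal.

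**The case against.** The strongest reply is that the article only names the events to be counted, and that the choice of denominator, per-patient or pooled summary and clustered interval belongs in an analysis plan that is not shown. Data analyses allows percentages, programme adherence and exercise frequency will be reported alongside, and session-level logbooks let anyone form a rate later. The article also says that its adherence definitions are based on a published source, which is not at hand and may supply a denominator.

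Part of this stands. Nothing is lost irrecoverably, and the omission of a detailed analysis method would be no finding. But the article does state a definition for each outcome, and that definition is a count, next to two measures in the same list that are percentages. A generic mention of percentages does not change it. Programme adherence can serve the start-time evaluation for attendance, but not for modification or early stopping.

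Four stronger readings should be resisted:

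- **Low counts show better tolerance.** A reader might infer this, or its converse. The Study intervention section makes adjustment by the patient a designed feature, so a modification is not simply intolerance.
- **40% of patients are expected to drop out.** The article calls its 60% retention figure conservative. It is a planning allowance, not a forecast.
- **The counts cannot be compared with other studies.** The documents do not show this, and using published definitions might help comparison.
- **The article plans to rank patients by these counts.** It does not say whether they are per-patient scores or cohort totals. Step 4 shows that the problem exists either way.

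**Conclusion.** The point holds. As defined, the three outcomes combine the frequency of modification or early stopping with the number of sessions prescribed and the time the patient stayed. They cannot by themselves support the evaluation by start time. The direction is certain: at a given rate, fewer sessions at risk means a lower count. The size rests on assumed schedules, stopping weeks and rates. Under those used here, exposure alone moves the count about 2.5-fold between completers at 2 and 5 sessions per week, and 4-fold between completing and stopping after week 2.

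The consequence is modest. These are descriptive secondary outcomes in a single-arm feasibility study with no planned hypothesis tests, and none of them is named in the Success criteria. The change is worth making because it is nearly free, not because the study's conclusions depend on it.

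**What to change.** Keep the counts and define each outcome as a proportion of sessions at risk:

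- **Pre-session modification:** modified sessions divided by sessions started. Sessions scheduled up to the date of withdrawal is an acceptable alternative; the full 8-week prescription is not.
- **During-session modification and early termination:** affected sessions divided by sessions started.

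Report per-patient percentages as median and interquartile range, and a pooled percentage with a 95% confidence interval that allows for repeated sessions within a patient. Give both overall and by start time (before, during or after treatment), with the number of sessions at risk beside each. Both summaries are useful: the pooled figure is dominated by patients with many sessions, while the per-patient figure gives equal weight to patients who contributed only a few. Add a sentence stating that a modification is use of the programme's built-in flexibility and is not in itself evidence of intolerance.

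The cost is wording only. Data collection methods already has patients log every session, prescribed sessions are already the denominator for programme adherence, and Table 3 lists a participant tracking log for retention.

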### Data collection methods

The two HaNC centres will keep logs on the number of eligible patients, and numbers screened, approached, and consented. Reasons for ineligibility will be recorded where relevant. Patient data will be recorded on case report forms, which will be checked for completeness and legibility before being entered into a trial database. Database entries will be checked for accuracy against the case report forms for all primary outcomes and 20% for secondary outcomes. If there are database errors in the primary outcomes, or greater than 1% errors for secondary outcomes, 100% data checks will be completed until the error rate ceases or drops.

Physical fitness tests will be standardised using a document that describes 1) the information to be given to patients at least 48 hours before arriving at the laboratory to prepare for the tests; 2) general safety precautions; 3) details of the standardised pre-test warm-up; and 4) how each test should be conducted, including the mandatory test order. The fitness test procedures are based on those described by Rikli and Jones [45] and Norkin and White [50]. Each patient will record the exercise intensity, duration, sets, and repetitions (as appropriate) of every exercise session in a logbook during the 8-week exercise programme. Patients also will record any adverse symptoms, other issues, and reasons for non-adherence. Patient demographic and characteristic data will be collected from patient medical records and include age, sex, ethnicity, history of smoking and alcohol consumption, tumour site and stage, human papillomavirus status, cancer treatment type, comorbidities, and body mass index. Socioeconomic status will also be determined using the participant’s full home postcode and reported as the English Index of Multiple Deprivation score.

A summary of the data collection methods to address each of the study’s objectives is shown in Table 3.

**Table 3 pone.0289911.t003:** Methods for collecting data for each study objective.

Study objective	Method of recording
Eligibility, exercise programme uptake, retention, and different aspects of exercise adherence.	Screening logs, patient participant tracking log, and patient participant logbooks.
People with HaNC, health professionals’, and cancer exercise specialists’ views on acceptability, intervention components, processes, and feasibility of integrating the intervention into the usual care pathway.	Qualitative analysis of semi-structured interviews.
Intervention and participant fidelity.	Intervention fidelity: Completion of a checklist for each patient participant used to scrutinise exercise programmes and logs completed by the cancer exercise specialists. Another checklist will be used to document the training and support received by the cancer exercise specialists. Participant fidelity: Scrutiny of the participants’ logbooks after exercise programme completion.
Frequency, intensity, duration, type, and location of exercise, and timing of the start of the exercise programme, based on the current needs, preferences, and goals of people with HaNC.	Self-reported by patient participants in their exercise programme logbook.
Suitability of outcome measures and provide data to allow a sample size calculation for a definitive RCT.	Quantitative data and qualitative analysis of semi-structured interviews.

**HaNC** = head and neck cancer.

### Fidelity

Intervention fidelity will be determined using a checklist for each patient. Completion of this checklist will be facilitated by scrutinising exercise programmes and logs completed by the cancer exercise specialists. The logs will include meetings notes and records of texts sent to each participant. Another intervention fidelity checklist will be used to document the training and support received by the cancer exercise specialists. Participant fidelity will be determined by scrutiny of the participants’ logbooks after exercise programme completion.

### Interviews

Acceptability of the intervention will be explored by qualitative semi-structured interviews with approximately 20 of the participants with HaNC, purposively sampled to ensure maximum variation based on gender, age, socio-demographic characteristics, location, type of cancer treatment, and where possible, those that declined to participate. Patients who decline, withdraw from, postpone, or complete the intervention will be invited to participate in an interview. Purposive sampling will aim to capture patients at different time points (i.e., both during and after completion of the programme) and patients with different levels of adherence to the intervention. Feasibility of integrating the intervention into the usual care pathway will be explored by qualitative semi-structured interviews with up to 20 healthcare professionals involved in the care of the people with HaNC at the two study sites, and the cancer exercise specialists. The focus will be on assessments and programme delivery, usability of the study materials and intervention tools, and acceptability of the content and timing of the intervention. All interviews will be conducted by an experienced qualitative researcher with skills in interviewing vulnerable populations around sensitive topics. Informed consent will be sought prior to interview. Interviews will be audio-recorded. A topic guide will be used in the interviews, but interviewees will be encouraged to speak freely about any other issues relating to the feasibility and acceptability of the intervention. The topic guide has been developed from discussions within the wider research team, the CHANGE PPI group, and from literature around exercise participation. The guide will be revised as new issues emerge in each interview. Each interview is expected to last between 40 and 60 minutes.

Triangulation. Quantitative and qualitative data on patients’ and healthcare professionals’ engagement with the intervention, will be regularly discussed and triangulated at project management group meetings to identify ways to refine the intervention and study processes while the study is ongoing. The impact of these refinements will then be examined both qualitatively and quantitatively. Procedurally, the “following a thread” framework for triangulation and integrative analysis of qualitative and quantitative data will be adopted. There is no assumption over the primacy of either data type and will look for both convergences and divergences between them and aim to produce categories and themes that accommodate both types of data. Attention to exploring any divergences between the quantitative and qualitative data will be given, as these can often provide important insights. This will generate insights about ways of personalising the intervention to the needs and preferences of different patient groups, understanding variation in engagement and outcomes of the intervention, and provide insights on the mechanisms by which the intervention has an impact.

